**Objectives:**

The primary objectives of this study are to (1) identify risk factors for vessel perforation, (2) explore the underlying pathophysiology, (3) develop a classification system for vessel perforations, (4) compare different hemostatic treatment strategies, (5) evaluate the impact of continuing versus aborting thrombectomy after perforation, and (6) propose a safety-optimized thrombectomy technique.

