The available data on vessel perforations during thrombectomy are limited (21). It is unknown why some patients experience this complication, while the majority are spared. Similarly, the underlying pathophysiological process that leads to vessel wall damage is not understood. There is uncertainty about which patients benefit from endovascular hemostatic treatment to achieve cessation of active bleeding and whether temporary vessel occlusion (e.g., using an intracranial balloon catheter or by deploying coils without detachment) or permanent vessel occlusion (e.g., using liquid embolic agents or permanent coiling) is more appropriate. In addition, limited data are available on whether thrombectomy should continue after a perforation occurs or whether the procedure should be aborted. Given the low frequency of this complication and its hyperacute nature, randomized prospective trials are unlikely to be feasible.

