## Methods and analysis

### Design

The Perforation EVents during ENdovascular Therapy for acute ischemic stroke (PREVENT) Registry is an international, multicenter, prospective, and retrospective observational study collecting data on vessel perforations during thrombectomy.

Data collection includes the following:

Patient baseline data (e.g., age, sex, pre-stroke modified Rankin Scale (mRS), pre-stroke anticoagulation or platelet therapy, and others).Data on the initial ischemic event (e.g., NIHSS at admission, number and location of vessel occlusions, TOAST classification [trial of ORG 10172 in Acute Stroke Treatment], imaging features related to clot composition, intracranial atherosclerotic disease (ICAD) or primary intracranial dissection, non-interventional stroke management, and other relevant factors).Details on circumstances and technique of the thrombectomy (e.g., anesthesiological management, type of aortic arch, cervical stenosis, thrombectomy technique, design and dimensions of the thrombectomy devices, operator experience, and others).Hemostatic therapy (e.g., non-endovascular hemostatic measures such as lowering of the systemic blood pressure or medication with coagulation effects, endovascular hemostatic measures including timing, exact mechanism, effectiveness, and other relevant factors).Outcome measures (e.g., functional outcomes including mRS at 90 days, and imaging outcomes including recanalization status, volume of intracranial hemorrhage, and other relevant factors).

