Which risk factors are associated with the occurrence of vessel perforations during thrombectomy?Is it possible to identify distinct mechanisms of vessel perforation? Is it possible to describe pathophysiological phenomena associated with vessel perforation?Are there groups of perforations that can be distinguished in terms of risk profiles and the need for urgent complication management, on the basis of which a classification system can be created? If so, can a pathophysiological explanation be found for the differences between these groups?In patients with ongoing contrast extravasation, which individuals should receive endovascular therapy to achieve hemostasis? How do specific hemostatic strategies compare to others regarding efficacy and safety?In patients in whom ongoing contrast extravasation has stopped, should thrombectomy be continued, or should the procedure be aborted?Based on the insights gained from PREVENT, is it possible to design a safety-optimized thrombectomy technique that may be used if patient-related risk factors imply an increased risk of vessel perforation?

Figure 1 shows the aims of the PREVENT registry.

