### Data analysis

Summary tables for patient demographics as well as baseline and intervention characteristics will be provided. Further statistical analysis will be tailored for each of the study’s aims. The methods per aim are presented below, following the same order:

To identify risk factors associated with vessel perforations, we will, in the first stage, make comparisons between cases with and without perforation during thrombectomy for predefined risk factors. Statistical analyses will include paired samples *t*-test, Wilcoxon test, and chi-squared test or Fisher’s exact test. Furthermore, multivariable logistic regression models can be used to identify the association between multiple variables and the occurrence of vessel perforations.An exploratory analysis of the interventional image material in the central image analysis laboratory is planned. After reviewing the image material of approximately 20% of patients with explorative intention, imaging criteria will be defined with regard to possible mechanisms of vessel wall injury and distinct pathophysiological phenomena. These criteria will be used to classify the remaining 80% of patients. Due to the exploratory nature, no definitive statistical evaluation strategy can yet be determined.For this purpose, data-driven K-nearest neighbor clustering will be applied to identify different groups of similar patient characteristics. We will consider 2–4 clusters, and the distribution of the clusters will be inspected visually. After the identification of the clusters, we will compare the pathophysiological characteristics between the clusters.Patients with perforation will be divided into two groups: patients who received interventional hemostatic therapy after the perforation occurred—e.g., temporary intracranial balloon occlusion or permanent vessel occlusion with liquid embolization or coils—and patients who did not receive hemostatic therapy. Propensity score matching or inverse probability of treatment weighting will be used to control for the location of perforation and the flow rate of extravasation. The two groups will be compared with each other to identify differences in the duration of extravasation and in clinical outcomes. The appropriate statistical model will be used for each of the clinical outcomes (e.g., logistic regression model for binary outcomes and ordinal regression model for ordinal outcomes).Patients with perforation will be divided into two groups: patients in whom thrombectomy was continued after the perforation occurred and patients in whom the procedure was aborted. Propensity score matching or inverse probability of treatment weighting will be used to control for the amount of extravasation, stroke severity, occlusion location, collateral status, and other clinical outcome predictors. The two groups will be compared with each other to identify differences in clinical outcomes.The new insights on risk factors, mechanisms, and pathophysiology of vessel perforation will be gathered. An expert panel will discuss potential modifications to current thrombectomy workflows to reduce the risk of periprocedural perforation, both in response to specific patient-related risk factors (e.g., occlusion location and vessel tortuosity) and in general. No definitive statistical evaluation strategy can yet be determined.

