By focusing exclusively on vessel perforations during thrombectomy, the PREVENT registry represents a dedicated effort to target a specific safety aspect of thrombectomy. Unlike prospective randomized trials, which would be unfeasible due to the rarity and acute nature of this complication, PREVENT allows for the collection of a large, real-world dataset across multiple institutions. The matched case–control approach enables comparisons between patients with and without perforation under otherwise similar conditions. This may help to identify characteristics of the patient (e.g., neurovascular risk factors), the procedure setting (e.g., anesthesiologic strategy), or the devices (e.g., dimensions in relation to vessel diameters) that might be associated with increased risks. Additionally, the centralized imaging analysis ensures a standardized interpretation of angiographic and postprocedural imaging, allowing for the identification of distinct pathophysiological patterns of vessel perforation. A comparison between different hemostatic strategies (e.g., medical management only, temporary vessel occlusion, and permanent vessel occlusion) may provide insights into their effectiveness. By leveraging data that have been previously collected in routine clinical practice, PREVENT circumvents ethical and logistical barriers inherent in interventional trials while still providing robust insights into the mechanisms, management, and potential prevention of vessel perforations in thrombectomy.

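### Aim 4 promises a comparison between hemostatic strategies, but its only described analysis pools temporary and permanent occlusion into one group

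*Protocol article*

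**What the plan says.** **What is promised.** Objective 4 in the Abstract is to "compare different hemostatic treatment strategies". Question 4 in the Design section has two halves. The first asks "which individuals should receive endovascular therapy to achieve hemostasis". The second asks "How do specific hemostatic strategies compare to others regarding efficacy and safety". The Introduction gives the reason: it is uncertain whether "temporary vessel occlusion (e.g., using an intracranial balloon catheter or by deploying coils without detachment) or permanent vessel occlusion" is more appropriate. The Discussion names the strategies to be compared as "medical management only, temporary vessel occlusion, and permanent vessel occlusion".

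**What is planned.** The Data analysis section states that it gives the methods aim by aim, in the order of the aims. For aim 4 it forms two groups from the perforation cases. One is any interventional hemostatic therapy, with the examples "temporary intracranial balloon occlusion or permanent vessel occlusion with liquid embolization or coils". The other is "patients who did not receive hemostatic therapy". Propensity matching or weighting is to control for perforation location and extravasation flow rate. The two groups are then compared on duration of extravasation and clinical outcomes.

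**What is collected.** The Design section lists "non-endovascular hemostatic measures such as lowering of the systemic blood pressure or medication with coagulation effects" under hemostatic therapy, along with the timing, exact mechanism and effectiveness of endovascular measures.

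**The concern.** The two strategies whose relative merit the Introduction calls uncertain sit in the same arm of the only contrast described. If that contrast is carried out as written, objective 4 and the second half of question 4 get no answer, even though the registry holds the data to address them.

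The pooled result could also mislead. A difference near zero might be read as showing that endovascular hemostasis makes no difference, when it may average unlike effects. A clear difference might be credited to both strategies when it comes from one. The result would also shift with the mix of techniques at the contributing centers.

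A smaller point concerns the comparison group. The Design section and the Discussion treat medical measures as hemostatic therapy, so the label does not say plainly where a patient managed only with blood-pressure lowering or drugs belongs.

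**Working it through.** The article gives no effect size, power or group size for aim 4, so there is no figure to reproduce. The check is mainly textual, with an illustration.

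**1. Match of promise and analysis.**

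| Stated purpose | Contrast needed | In the Data analysis section? |
|---|---|---|
| Question 4, first half: who should get endovascular hemostasis | interventional vs not | Yes, as a two-group contrast |
| Question 4, second half, and objective 4 | strategy vs strategy | No |
| Introduction: temporary or permanent occlusion | temporary vs permanent | No, both are in one group |
| Discussion: medical only, temporary, permanent | three-way | No, temporary and permanent are merged |

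**2. Why the pooled contrast cannot stand in.** Let *t* be the share of interventional patients treated with temporary occlusion, and let δT and δP be the effects of temporary and permanent occlusion against the comparison group. Then

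pooled difference = t·δT + (1 − t)·δP.

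This is one equation in two unknowns. A pooled value of 0 at t = 0.5 fits δT = δP = 0 and equally fits δT = −10, δP = +10 points. Opposite signs are not required: with δT = −10 and δP = 0, the pooled difference is −3 points at t = 0.3 and −7 points at t = 0.7.

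**3. Illustration.** From the document: 500 cases and mortality of about 50%, used here as the comparison-group rate. Assumed: 250 of 500 interventional (range 30–70%), *t* from 0.3 to 0.7, and equal and opposite mortality shifts of *d* = 10 points (range 10–20). The direction assigned to each strategy is arbitrary. The pooled difference is (1 − 2t)·d. Power (two-sided 5%, unadjusted) is

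Φ{[|p1 − p2| − 1.96·√(p̄(1 − p̄)(1/n1 + 1/n2))] / √(p1(1 − p1)/n1 + p2(1 − p2)/n2)}.

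For 125 vs 125 at 40% vs 60%: (0.20 − 1.96 × 0.0632)/0.0620 ≈ 1.23, which gives 89%.

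| t | Pooled difference | Power, pooled | Temporary / permanent n | Power, temporary vs permanent |
|---|---|---|---|---|
| 0.3 | +4 points | 14% | 75 / 175 | 83% |
| 0.5 | 0 | 5% (2.5% per tail) | 125 / 125 | 89% |
| 0.7 | −4 points | 14% | 175 / 75 | 83% |

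Over the whole assumed range, pooled power runs from 2.5% (single tail) to 43%, and power for temporary versus permanent from 62% to over 99%.

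**4. Price in precision.** The 95% half-width at 50% mortality is 1.96·√(0.25(1/n1 + 1/n2)):

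- pooled, 250 vs 250: 8.8 points
- one strategy vs none, 125 vs 250: 10.7 points
- temporary vs permanent, 125 vs 125: 12.4 points (10.5 at 175 vs 175, 17.5 at 45 vs 105)

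Weighting widens these. If it cost 20% to 50% of the effective sample (an assumption), 12.4 would become 12.4/√0.8 = 13.9 to 12.4/√0.5 = 17.5 points.

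**The case against.** The strongest reply is that this is a journal article condensing a fuller protocol. It says the analysis will be tailored to each aim, names the three-way comparison in the Discussion, and collects mechanism and timing. Nothing excludes contrasts by strategy, and a pooled contrast is a legitimate answer to the first half of question 4. That last part stands, and it is why the pooled contrast should be kept. The rest does not remove the point. The section fixes an exposure definition that does not match the objective, and for aims 2 and 6 it says that no definitive evaluation strategy can yet be set. It makes no such reservation for aim 4.

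Three stronger readings are tempting, and the documents do not support them:

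- *Medically managed patients fit neither group, so the comparator contradicts itself.* This takes the label of the second group literally. The text divides the cases into two groups, the first defined by interventional therapy, and the first half of question 4 asks about endovascular treatment. The natural reading is interventional versus not, with one adjective missing.
- *Opposite effects will cancel.* The documents report no effect by strategy. Exact cancellation needs equal and opposite effects and an equal mix, which were chosen here to show the mechanism.
- *The registry cannot make the comparison.* The data are collected. What is lacking is an analysis that uses them.

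It is also fair to object that the power figures ignore adjustment. They are unadjusted and overstate what a weighted analysis would achieve.

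**Conclusion.** The point holds in a limited form and should be corrected before analysis. The aim-4 method described in the Data analysis section addresses at most whether endovascular hemostasis was used, and it leaves objective 4 and the second half of question 4 without a matching analysis. This follows from the text alone and needs no assumed numbers.

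How much the pooling would hide is unknown. The 0-to-4-point pooled differences against a true 20-point gap between strategies (two shifts of 10 points) rest on assumed effects, mix and group sizes. They show what could happen and are not a forecast. The group-2 label is an ambiguity to tidy up, most likely meant as no interventional hemostatic therapy. Even on that reading, medically managed and untreated patients share one group, so medical management is not examined as a strategy in its own right.

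**What to change.** In the Data analysis section, for aim 4:

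1. Keep the pooled contrast, tie it to the first half of question 4, and reword the second group as *no interventional hemostatic therapy*.
2. Add three contrasts for the second half: temporary versus permanent occlusion, temporary versus no interventional hemostasis, and permanent versus no interventional hemostasis. Estimate them with a multi-category propensity score and weighting, extending the method already planned.
3. Classify patients by the first strategy applied, and report escalation from temporary to permanent occlusion separately.
4. Report medical measures only versus no hemostatic measure separately where numbers allow.

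The cost is analysis wording and some extra modeling. No new data are needed, since mechanism and timing are already collected. Each pairwise contrast is less precise than the pooled one (in the illustration, a half-width of about 12 instead of 9 points before weighting), and weighting lowers precision further. If one strategy turns out to be rare, its contrasts may be only descriptive.

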**Design:**

The Perforation EVents during ENdovascular Therapy for acute ischemic stroke (PREVENT) Registry is an international, multicenter, prospective, and retrospective study, collecting data on vessel perforations during thrombectomy. The registry aims to include 500 cases of vessel perforation and 500 matched controls without perforation. The collected data will consist of both tabulated data and periprocedural imaging, which is to be analyzed centrally by an imaging core laboratory. Data will be analyzed using a case–control method, employing both univariate and multivariate statistical analyses.

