## Introduction

Stroke is the second leading cause of death and the leading cause of disability, both globally and in Europe (1, 2). Thrombectomy has revolutionized the treatment of acute ischemic stroke, following evidence from five randomized controlled trials demonstrating a substantial benefit in patients with large-vessel occlusion of the anterior circulation (3). Since then, the indications for thrombectomy have continued to expand (4), including patients with posterior circulation occlusions (5, 6), selected patients presenting late after symptom onset (7–9), and patients with large infarcts (10, 11). Patients with medium or distal vessel occlusions (MDVOs) are also increasingly being considered for thrombectomy (4, 12, 13). Two recent randomized controlled trials did not demonstrate the superiority of MDVO thrombectomy over best medical treatment alone (14, 15). One trial reported a higher number of symptomatic intracranial hemorrhages (sICHs) and a higher mortality in the thrombectomy group (14). A third trial was stopped early for futility and also reported a higher rate of sICH in the thrombectomy group compared to the best medical management group (16).

These findings might point towards a different aspect of thrombectomy: despite its effectiveness, the procedure is not without the risk of periprocedural complications. Intracranial vessel perforation with subsequent arterial bleeding occurs in 1–6% of thrombectomies (17–20). This complication is typically a critical event, with permanent consequences (21, 22) and a mortality rate of approximately 50% (17, 19, 23). Given the rapidly increasing number of thrombectomies, an increase in the incidence of periprocedural perforations is to be expected. This is particularly relevant for MDVO thrombectomy, as the incidence of vessel perforations has been reported to be twice that of LVO thrombectomy (17).

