### Selection/treatment of subjects

Adult patients (≥18 years) who underwent thrombectomy for acute ischemic stroke on or after 1 January 2015 and experienced a periprocedural vessel perforation will be included. Vessel perforation is defined as contrast extravasation in at least one angiography series. Patients will be excluded if intracranial hemorrhage was present on pre-interventional imaging, if vessel wall damage was due to intracranial dissection without active contrast extravasation, if vessel perforation was due to the rupture of a pre-existing intracranial aneurysm (i.e., extravasation originates from an aneurysmal outpouching or dilation of an intracranial artery on the first run that demonstrates extravasation), or if vessel perforation led to the development of an arteriovenous fistula (e.g., carotid-cavernous fistula), but not to subarachnoid hemorrhage.

To evaluate risk factors that predispose patients to perforations, PREVENT is designed as a case–control registry. For the inclusion of each patient who experiences a perforation during thrombectomy, one matched patient of the same sex and similar age, with acute ischemic stroke due to vessel occlusion in the same vascular segment and treated at the same center, but without perforation, will be included.

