
## Discussion

Randomized controlled trials have established the efficacy of thrombectomy, providing a strong foundation for guideline recommendations (3, 5, 6, 8–11). However, as materials and interventional strategies continue to evolve, thrombectomy techniques are constantly being refined. Enhancing the safety of thrombectomy presents a unique challenge: prospective trials are typically not designed to detect complications that occur at low frequencies. However, these complications can be severe, often carrying profound or even fatal consequences for affected patients (17–19, 21, 23). Therefore, efforts to improve thrombectomy should focus not only on optimizing reperfusion but also on preventing complications whenever possible and enhancing complication management strategies. This becomes even more crucial given the expanding indications for thrombectomy. The net benefit of thrombectomy is presumed to be lower in patients with low National Institutes of Health Stroke Scale (NIHSS) scores at presentation or those with medium or distal vessel occlusions (MDVOs) than in the HERMES meta-analysis cohort. While minimizing adverse events is always important, the impact of severe complications may be even more pronounced in these patient populations since the natural course of disease is less severe. Consequently, improving procedural safety could help extend thrombectomy indications to patients who might otherwise be excluded due to safety concerns.

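### Aim 4 adjusts for two perforation variables only, so differences in era or enrolment mode could be mistaken for an effect of hemostatic therapy; aim 5 should name both variables

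*Protocol article*

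**What the plan says.** The Design section describes an "international, multicenter, prospective, and retrospective observational study collecting data on vessel perforations during thrombectomy". Under Selection/treatment of subjects, eligible cases are adults "who underwent thrombectomy for acute ischemic stroke on or after 1 January 2015 and experienced a periprocedural vessel perforation". No end date or period stratum is given.

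In Data analysis, aims 4 and 5 each split all patients with perforation into two groups, without separating them by period or enrolment mode.

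- **Aim 4** (hemostatic therapy or none): "Propensity score matching or inverse probability of treatment weighting will be used to control for the location of perforation and the flow rate of extravasation".
- **Aim 5** (thrombectomy continued or aborted): the same methods are to "control for the amount of extravasation, stroke severity, occlusion location, collateral status, and other clinical outcome predictors".

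The main Discussion section remarks that "as materials and interventional strategies continue to evolve, thrombectomy techniques are constantly being refined".

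**The concern.** Aims 4 and 5 compare groups within the cases. The matching on sex, age, vascular segment and center links cases to controls, so it gives these comparisons no protection. They depend on the propensity model alone.

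Two features could differ across the covered years.

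- **Practice and case mix.** The article says that techniques keep changing, and its Introduction says that indications have widened to late presenters, large infarcts and more distal occlusions. Prognosis after a perforation may therefore shift with calendar time. Aim 4 does not list stroke severity, which might have captured part of such a shift.
- **Case capture.** Retrospective cases can be identified once management and outcome are known. Severe events may be easier to find that way.

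If either feature is related both to receiving hemostatic therapy and to outcome, the aim 4 estimate mixes it with the treatment effect. The article considers randomized trials of this question infeasible, so a biased estimate is unlikely to be corrected by a trial later.

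**Working it through.** **Comparison of the two adjustment lists.** Aim 4 names two variables and stops. Aim 5 names four and adds an open category of outcome predictors. The authors left one list open and not the other, so the aim 4 set reads as a stated choice. Procedure year and enrolment mode are named in neither.

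**Size.** The article gives no figure to reproduce here, so this is an illustration.

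Inputs from the article: 500 cases (Abstract, Design) and mortality after perforation of about 50% (Introduction). Assumed inputs: everything that differs between the strata.

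Let *s* be the retrospective share, *t*R and *t*P the proportions receiving hemostatic therapy in retrospective and prospective cases, and *m*R and *m*P the mortality in each. Treatment has no effect within either stratum.

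- Retrospective share among treated: *q*T = *s t*R / [*s t*R + (1−*s*) *t*P]
- Retrospective share among untreated: *q*U = *s*(1−*t*R) / [*s*(1−*t*R) + (1−*s*)(1−*t*P)]
- Spurious risk difference: RD = (*m*R − *m*P)(*q*T − *q*U)

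*Scenario A:* *s* = 0.5, mortality 55% and 40%, therapy 30% and 60%.

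- *q*T = 0.15/0.45 = 0.333; *q*U = 0.35/0.55 = 0.636
- RD = 0.15 × (0.333 − 0.636) = −0.045, that is, 45.0% versus 49.5%, OR 0.83

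*Scenario B:* *s* = 0.5, mortality 55% and 45%, therapy 30% and 50%.

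- *q*T = 0.15/0.40 = 0.375; *q*U = 0.35/0.60 = 0.583
- RD = 0.10 × (0.375 − 0.583) = −0.021, that is, 48.7% versus 50.8%, OR 0.92

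Over both scenarios, with *s* from 0.3 to 0.7, RD runs from −1.7 to −4.5 points.

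**Effect on the test.** Take 500 cases, two equal strata, overall mortality 50%, half the cases treated, and a two-sided 5% Wald test:

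| Therapy, early vs late | Mortality gap, early minus late | RD (points) | OR | False-positive rate |
|---|---|---|---|---|
| any | 0 | 0 | 1.00 | 5% |
| 50% vs 50% | any | 0 | 1.00 | 5% |
| 40% vs 60% | 10 points | −2 | 0.92 | 7% |
| 30% vs 70% | 10 points | −4 | 0.85 | 15% |
| 30% vs 70% | 20 points | −8 | 0.73 | 43% |

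For scale, 250 versus 250 has 80% power for a 12.5-point difference around 50%. Once the stratum enters the propensity model, the spurious difference in this set-up is zero by construction.

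**The case against.** Five points can be made against this.

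- **The article is condensed.** Full covariate lists and sensitivity analyses are commonly left to a fuller document, which is not shown. The aim 4 list is not declared exhaustive. This limits the weight of the point but does not remove it: the article does state what aim 4 controls for, and it closes that list while leaving the next one open.
- **Severity is partly adjusted already.** The Design section uses the flow rate of extravasation as a stand-in for the size of the perforation, graded centrally, and aim 4 adjusts for it. This stands. The calculation above ignores that adjustment, so it probably overstates the part of the bias that runs through severity.
- **Drift is not documented.** The Discussion remark concerns thrombectomy techniques and materials. It does not say that the use of hemostatic therapy changed. Nor does any section describe how retrospective and prospective cases are found. This also stands, so the point must be conditional.
- **Aim 5 is open.** A reader might infer that aim 5 also omits adjustment for era and enrolment mode. The wording does not support that, because its open category can include anything that predicts outcome.
- **The two variables may overlap.** If prospective cases are mostly recent ones, balancing on both could be difficult. The fix allows for this.

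**Conclusion.** The point holds for aim 4, conditionally. As stated, its adjustment leaves era and enrolment mode uncontrolled in a comparison that the case-control matching does not protect. For aim 5 it is only a request to name the two variables.

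A reader might go further and infer that era differences will show up as treatment effects, or that the strategy used more in later years will look better. The documents support neither. Bias needs era or enrolment mode to relate to both treatment and outcome, and no data are given on either link. The direction in the illustration follows from assuming higher mortality in the retrospective cases and more therapy in the prospective ones.

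The figure of about 2 to 4.5 points is therefore illustrative. It rests on assumed shares, mortality and treatment rates, and it leaves out the planned adjustment. This is a worthwhile, inexpensive improvement rather than a demonstrated error in a result.

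**What to change.** 1. Add procedure year (spline or era bands) and enrolment mode to the aim 4 propensity model.
2. Name both variables in the aim 5 list.
3. Check balance on both after matching or weighting. If they overlap too heavily, keep year in the model and examine enrolment mode in the sensitivity analysis.
4. Prespecify a sensitivity analysis of each comparison restricted to prospectively enrolled cases. Adjusting for enrolment mode does not remove outcome-dependent selection within the retrospective cases, so step 1 alone is not enough.

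The cost is a change of wording, one or two more propensity terms, and a prospective-only estimate that is less precise than the pooled one. The registry should already hold the procedure date and enrolment mode for each case, although the article does not say so explicitly.
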